#### Control Condition

When clinics are in the control condition, participants will receive care as usual.

#### Study Measures and Outcomes

In the baseline survey, participants are assessed for past SRH care receipt [10]; sexual behavior, including condom use [39,40]; SRH knowledge [35,36]; self-efficacy related to condom use [37] and talking to clinicians about SRH [38]; and background characteristics [10] (Table 1). At the first follow-up survey (48 hours after the visit), participants were assessed for SRH care receipt at the clinic visit, visit satisfaction, quality care receipt [41], and SRH knowledge and self-efficacy and, for participants in the intervention phase, acceptability [33,34], usability [32], and satisfaction [33] using the Health-E You app. At the second follow-up survey 2 months later, participants are assessed for the same baseline measures, including method use behaviors, and any additional app engagement (Table 1).

#### Retention

Strategies for participant retention from baseline through the follow-up surveys include participant remuneration, collecting multiple contacts at baseline and subsequent follow-ups (ie, phone number, email, etc), check-ins with participants between surveys, advising and providing US $5 gift cards to participants contacting us with changes in contact information, and sending reminder messages before conducting follow-up procedures [14,40].

#### Power and Sample Size

We generated power analyses using NCSS PASS 16 to compute minimum detectable effect sizes for condom use at last intercourse [40]. Assuming 2064 participants at the 2-month follow-up (86 participants per clinic per assessment), α of .05, power of .80, and an intracluster correlation coefficient of 0.06 (calculated from previous Health-E You data with female individuals [14]) with a baseline prevalence of 61.1% condom use at last intercourse [40], the minimum detectable difference is 12.2 percentage points, which translates to an effect size (h) of 0.26, just above the accepted threshold for a small effect size of 0.20. A baseline sample of 2752 participants (approximately 115 participants per clinic per step) will be recruited to account for 79.9% (2201/2752) retention at immediate follow-up (48 hours) and 75% (2064/2752) retention at 2-month follow-up.

#### Efficacy Trial Statistical Analysis

The main effects of the Health-E You intervention are being estimated using an intention-to-treat approach using separate mixed models for each study outcome, with a random intercept to reflect clustering of patients within clinics and adjustment for clinic size [49]. Each model estimates differences between the intervention and control arm in the change in each study outcome between baseline and each follow-up. This type of analysis allows for examining (1) within-individual change over time in an outcome, accounting for dependency among observations within individuals by modeling within-person error [50]; (2) between-individual variation over time [51]; and (3) between-subjects effects based on group assignment to identify significant differences in Health-E You versus usual care. We will also assess the potential moderating effect of patient demographics and adolescents’ visit reason, which may influence SRH care receipt, on the study’s outcomes. We are addressing incomplete data with maximum likelihood and multiple imputations [52-54]. The use of these missing replacement strategies does not mitigate loss of statistical power but does minimize bias because of attrition [55].

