### Stage 2: Efficacy Trial

#### Efficacy Trial Setting

We will conduct the efficacy trial of Health-E You at 8 primary care settings that serve male adolescents aged 13 to 21 years from November 2025 for approximately 2 years. We recruited participating clinics through professional medical organization outreach and existing relationships. This trial has been registered on ClinicalTrials.gov (NCT06525064).

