#### Stepped-Wedge Evaluation Design

We will evaluate the app’s efficacy using a cluster randomized controlled stepped-wedge design, a one-way crossover design in which all clinics will begin the study in the control phase and then transition to the Health-E You intervention [44]. This design was chosen because it allows all sites to receive the intervention over the study course. Clinics will be stratified by adolescent patient population size (large versus small) and randomized into clusters within each stratum, which will dictate when they transition to the intervention phase during the 28-month study period.

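### The clinic random intercept drops out of the stated difference-in-change contrast, so the model makes no allowance for clinics differing in change between periods or in treatment effect

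*Protocol article*

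**What the plan says.** All references are to the protocol article.

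- **Random structure** (Efficacy Trial Statistical Analysis): the main effects are estimated "using separate mixed models for each study outcome, with a random intercept to reflect clustering of patients within clinics", "and adjustment for clinic size". The repeated surveys are handled by "accounting for dependency among observations within individuals by modeling within-person error".
- **Target** (same section): "Each model estimates differences between the intervention and control arm in the change in each study outcome between baseline and each follow-up".
- **Design** (Stepped-Wedge Evaluation Design; Efficacy Trial Setting): "a one-way crossover design in which all clinics will begin the study in the control phase and then transition to the Health-E You intervention". "We will conduct the efficacy trial of Health-E You at 8 primary care settings".
- **Sample size** (Power and Sample Size): "Assuming 2064 participants at the 2-month follow-up (86 participants per clinic per assessment"), with "an intracluster correlation coefficient of 0.06" and a detectable difference of 12.2 percentage points from a baseline of 61.1%.

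The only random term named at clinic level is the intercept. Clinic size enters as a fixed adjustment.

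**The concern.** The random intercept is the one term offered to deal with clustering, but the quantity estimated is a difference in change. A clinic that is always 10 points above the others is 10 points above at baseline and at follow-up, so its level disappears when follow-up is compared with baseline. What remains uncertain at clinic level is whether clinics change by different amounts in different periods, or respond differently to the app. The stated model has no term for either.

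Such variation is plausible here. The patient summary reaches the clinician by email or by printing at the clinic, according to local workflow (Health-E You Intervention Condition), and monthly reports are used to address clinic barriers to sharing it (Quality Control Process Monitoring). Recruitment runs for about 2 years.

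What is at stake is whether the nominal .05 level and the confidence intervals can be trusted for every outcome modelled this way.

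**Working it through.** **1. Layout.** 2064 / (8 × 86) = 3, so each clinic contributes three periods of 86. The article does not state the number of steps. I take 3 periods, with 4 clinics crossing at each of 2 steps.

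**2. Reproducing the plan's own figure.** The Hussey-Hughes variance is Iσ²(σ² + Tτ²) / [(IU − W)σ² + (U² + ITU − TW − IV)τ²].
- Total variance: 0.611 × 0.389 = 0.2377. Between clinics: τ² = 0.06 × 0.2377 = 0.01426. Cell-mean error: σ² = 0.94 × 0.2377 / 86 = 0.002598.
- For this layout I = 8, T = 3, U = 12, W = 80 and V = 20. Hence IU − W = 16, and U² + ITU − TW − IV = 144 + 288 − 240 − 160 = 32.
- Variance = 8 × 0.002598 × (0.002598 + 0.04278) / (16 × 0.002598 + 32 × 0.01426) = 0.001894, so SE = 0.0435.
- Detectable difference = (1.960 + 0.842) × 0.0435 = 0.1219, or 12.2 points. The arcsine effect size for 61.1% versus 73.3% is 0.26. Both match the article.

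**3. Does the clinic intercept cancel?** Write the outcome of participant k in clinic i at time t as fixed effects + u_i + p_ik + e_ikt. The change from baseline is the change in fixed effects + (e_ikt − e_ik0); u_i is gone. Generalised least squares on the 8-clinic, 3-period layout, with clinic and participant effects, confirms this. The SE of the arm-by-time term is the same at clinic variance 0, 0.06 and 0.30. That holds with complete data and with 25% dropout unrelated to arm. A fixed main effect of clinic size cancels in the same way.

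**4. Size if clinics change differently by period.** Let ρ be the share of the variance of change that lies at clinic-period level. It is assumed, because the documents give none. A cell mean of 86 changes then has variance proportional to ρ + (1 − ρ)/86, while the model uses 1/86.
- SE ratio, true to model = √(1 + 85ρ).
- True type I error = 2Φ(−1.96 / √(1 + 85ρ)).

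| ρ (assumed) | 1 + 85ρ | SE ratio | True type I error |
|---|---|---|---|
| 0 | 1.000 | 1.00 | 5% |
| 0.001 | 1.085 | 1.04 | 6% |
| 0.002 | 1.170 | 1.08 | 7% |
| 0.005 | 1.425 | 1.19 | 10% |
| 0.01 | 1.850 | 1.36 | 15% |
| 0.02 | 2.700 | 1.64 | 23% |

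**5. Size if the variation is clinic-by-treatment.** Only clinic-periods under intervention carry the extra variance. With period effects in the model, the contrast on this layout rests on the middle period (4 clinics against 4). The squared ratio is ½(1 + 85ρ) + ½(1 − ρ) = 1 + 42ρ. At ρ = 0.01 and 0.02 the SE ratios are 1.19 and 1.36, and type I error is about 10% and 15%. Without period effects, type I error is about 13% and 21%. Either way it is below the clinic-by-period figure at the same ρ.

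**6. Secondary: the detectable difference.** The calculation in step 2 uses one constant clinic effect, that is, cluster autocorrelation 1. Splitting the same ICC of 0.06 into a constant and a period-specific part gives 15.0 points at autocorrelation 0.9 and 17.3 points at 0.8.

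**The case against.** **The harm is conditional.** A reader might infer that the confidence intervals are too narrow as a matter of fact. The documents do not support that. If clinics do not differ in change or effect, the SE is correct. Change is measured within the same participants over about 2 months, so stable clinic differences are already removed and ρ may be near zero. This stands, and it is why the range starts at 0.

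**The ICC of 0.06 cannot be put in for ρ.** The article states one ICC and does not say that it applies to change. Using it in step 4 would give a far larger error with no support in the text.

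**The intercept is not the only clinic-level term.** Clinic size is adjusted for. This is correct, but a fixed main effect does not help the contrast.

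**The form of the model is not settled.** Condom use at last sex is binary, and on a logit scale the cancellation is approximate. An intercept fitted to change scores would not cancel at all. Both points are fair. However, the article describes modelled within-person error across repeated surveys, which favours the longitudinal reading.

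**This is detail for an analysis plan.** Degrees-of-freedom methods and the full random structure are often left to a plan that is not shown, and their absence is not the point here. The article itself names both the clustering term and the estimand, and as stated the first does not serve the second.

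**Conclusion.** The point holds in conditional form. In a linear longitudinal model, the only clinic-level random term named in the article drops out of the effect it is meant to protect. The analysis then treats changes as if clinics did not matter, although clinics are randomised and there are 8 of them. If clinics differ in change by period, a share of only 0.5% to 2% of the change variance raises type I error to about 10% to 23%; at 0.1% to 0.2% it is about 6% to 7%, and at zero there is no error. Clinic-by-treatment variation of the same size does less damage.

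These figures rest on the inferred 3-period layout, equal cells of 86, a normal reference distribution and the assumed ρ. The 12.2-point detectable difference is not an arithmetical error: it reproduces, but only under a constant clinic effect. Should be fixed; moderate confidence.

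**What to change.** - Keep the clinic intercept. Add a clinic-by-period random effect (crossed with follow-up time where change is modelled), a clinic-by-treatment random effect, or both.
- Base inference on a method suited to 8 clinics: Kenward-Roger or Satterthwaite degrees of freedom, or a permutation test over the randomised crossover order within the clinic-size strata.
- Separately, report the detectable difference over a range of cluster autocorrelation rather than at 1 alone.
- If a fuller analysis plan already contains these terms, align the published description with it.

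The change is to wording and analysis code only; design and data collection are untouched. The cost is wider confidence intervals and a less favourable detectable difference.

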**Methods:**

This study consists of 2 stages. Stage 1 involves formative research, design, and user testing of Health-E You for male adolescents. Specifically, we implemented a youth-centered design process, using multiple rounds of qualitative data collection and engaging youth and clinician advisors to design the Health-E You app from April 2023 through April 2024. From May 2025, for approximately 6 months, we are conducting beta testing of the app with youth and its output with clinicians. Transcripts of interviews and focus groups from stage 1 will be analyzed using deductive and inductive thematic analysis to identify knowledge and skill gaps for the app to address as well as desired app features. Quantitative data will be analyzed using descriptive statistics. Stage 2 will involve a stepped-wedge cluster randomized controlled trial with 2752 participants in 8 primary care settings across the United States to assess the impact of Health-E You on sexually active male adolescents’ SRH care receipt and condom use. Data will be analyzed with an intention-to-treat approach using separate mixed models for each study outcome with a random intercept to reflect clustering of patients within clinics, adjusted for clinic size.

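### The stated stepped-wedge model has no calendar-period term, so drift that the baseline comparison does not remove, chiefly in care receipt at the visit, is partly counted as effect

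*Protocol article*

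**What the plan says.** Under Stepped-Wedge Evaluation Design, the protocol article describes "a one-way crossover design in which all clinics will begin the study in the control phase and then transition to the Health-E You intervention". Clinics are stratified by size and randomised to clusters, "which will dictate when they transition to the intervention phase during the 28-month study period". Efficacy Trial Setting gives 8 clinics and about 2 years.

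Efficacy Trial Statistical Analysis specifies separate mixed models for each outcome, "with a random intercept to reflect clustering of patients within clinics and adjustment for clinic size". The target is set in the next sentence: "Each model estimates differences between the intervention and control arm in the change in each study outcome between baseline and each follow-up". The Abstract (Methods) names the same terms: "with a random intercept to reflect clustering of patients within clinics, adjusted for clinic size". The time that this section discusses is each participant's survey time (T0, T1, T2). Neither place names step, period or calendar time.

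Power and Sample Size assumes 2064 participants at 2 months ("86 participants per clinic per assessment"), an ICC of 0.06, 61.1% condom use, alpha .05 and power .80, and reports a minimum detectable difference of 12.2 percentage points.

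**The concern.** In a one-way crossover, exposure is correlated with calendar time. What randomising the crossover order protects is the comparison between clinics that are in different conditions at the same calendar time. A model with only a clinic intercept also uses each clinic's before-after contrast, and with these inputs that contrast carries most of the weight. Clinic size is constant within a clinic and cannot absorb a time trend.

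Change from baseline helps only where T0 and follow-up measure the same thing and drift together:

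- **Care receipt.** Study Measures and Outcomes has T0 asking about past care and T1 about care at this visit. A change in clinic practice over the trial moves T1 without moving T0 equally.
- **Follow-up visit.** Table 1 shows no T0 measurement.
- **Condom use.** It is measured at T0 and T2, two months apart. Linear drift cancels, but seasonal or non-linear change over that window does not.

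At stake is a biased effect estimate and an inflated false-positive rate, mainly for care receipt, which the Abstract names first when it states what the trial will assess.

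**Working it through.** **Inputs.** From the protocol article: 8 clinics, 2064 analysed, 86 per clinic per assessment, ICC 0.06, 61.1%, alpha .05, power .80. Assumed: two-sided alpha; 3 periods, since 2064/(8 × 86) = 3; and 4 clinics crossing at each of 2 steps, so the sequences are 0,1,1 and 0,0,1. The number of steps is not stated.

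**1. Variance components.** Total variance 0.611 × 0.389 = 0.23768. Between-clinic τ² = 0.06 × 0.23768 = 0.01426. Cell-mean error σ² = 0.94 × 0.23768/86 = 0.002598.

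**2. The stated figure, with period effects (Hussey-Hughes).** Var = Iσ²(σ² + Tτ²) / [(IU − W)σ² + (U² + ITU − TW − IV)τ²], with I = 8, T = 3, U = 12, W = 16 + 64 = 80, V = 4×4 + 4×1 = 20.
- Numerator: 8 × 0.002598 × 0.04538 = 0.000943.
- Denominator: 16 × 0.002598 + 32 × 0.01426 = 0.4979.
- Var = 0.001894 and SE = 0.0435. Detectable difference = 2.80 × 0.0435 = **12.19 points**, matching the stated 12.2.
- Effect size: 2asin√0.733 − 2asin√0.611 = 0.261, matching the stated 0.26.

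**3. The same design without period effects.** Let c = τ²/(σ² + 3τ²) = 0.3143. The information on the treatment effect is (6 − 2c)/σ² = 5.371/0.002598, so SE = 0.0220 and the detectable difference is **6.2 points**.

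Other forms do not give 12.2. Averaged or pooled variance with period effects gives 11.7 to 11.8, schedules with 4 to 9 periods at the same total give 10.0 to 11.1, and parallel-cluster formulas give 14.0 to 22.8.

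**4. Bias when the true effect is zero, level comparison, no period term.** For a shift of 1 point per period (0, 1, 2), the expected coefficient is 8/(6 − 2c) = 8/5.371 = **1.49 points**.
- An assumed 2 points a year is 1.33 points per 8-month period (24 months in all) or 1.56 per 9.33-month period (28 months). Bias = 1.33 × 1.49 = 2.0, or 1.56 × 1.49 = 2.3 points.
- Divided by the SE of 2.20 points, that is 0.90 or 1.05 standard errors, so a nominal 5% test rejects in about 15% or 18% of trials.
- With 3 periods, 1.49/2 = 74% of a first-to-last linear rise enters the estimate. With 4 to 9 periods, 55% to 66% does.

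**5. The stated change model.**
- Linear drift acting equally on T0 and follow-up: bias zero.
- Drift in T1 care with a past-care baseline that does not move: in a simple difference in change the clinic intercept drops out (c = 0), and the factor is 8/6 = 1.33 points per 1-point shift. The bias is nearly that of the level comparison.
- Condom use, T0 to T2, using the weights of step 4: an accelerating 5-point rise gives 0.8 to 0.9 points, and a 12-month cycle of 5-point amplitude gives at most 1.9 to 2.7 points. With c = 0 these shrink by 1.33/1.49, about a tenth.

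**6. Precision of the change model with period and period-by-survey-time terms.** The change in a cell has variance 2σ²(1 − r), where r is the within-person correlation. Only the middle period has clinics in both conditions, giving a sum of squares of 8 × 0.25 = 2. So Var = σ²(1 − r), and the detectable difference is 2.80 × 0.05097 × √(1 − r) = 14.3√(1 − r) points.

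| r | Detectable difference (points) |
|---|---|
| 0 | 14.3 |
| 0.2 | 12.8 |
| 0.5 | 10.1 |
| 0.7 | 7.8 |

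It equals 12.19 at r = 1 − (12.19/14.28)² = 0.27. The document gives no value for r.

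**The case against.** The strongest defence is that the model contrasts change from each participant's own baseline. A reader might infer from the missing term that any secular or seasonal change is booked as effect, or that the trial becomes an uncontrolled before-after study. The document does not support either. Linear drift common to T0 and follow-up cancels for condom use, knowledge and self-efficacy. T1 is sent 48 hours after the visit, leaving little room for drift in knowledge or self-efficacy. Even a pure level comparison passes through only part of a trend. The 15% to 18% rates belong to level comparisons and do not describe condom use, the outcome on which power is based. All of this stands, and it confines the concern mainly to care receipt at T1 and the follow-up visit.

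It can also be said that the article is condensed, that it cites a source for the model, and that a power figure matching period adjustment suggests an incomplete description rather than a decision to omit the term. That is plausible, and a fuller analysis plan may contain it. But the article lists model terms in two places, down to clinic size. If period is in the full plan, both places misdescribe the analysis and need the same correction.

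Finally, the 3-period schedule is inferred and the trend sizes are assumed. Both are true. The direction of the bias does not depend on either, but its size does.

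**Conclusion.** The concern holds in limited form. As written, the model lacks the calendar-period term that a one-way crossover needs, and it does not match the power basis (12.19 points with period effects, 6.2 without, against 12.2 stated). Change that the baseline comparison leaves in place is partly counted as intervention effect. This applies chiefly to care receipt at the visit and the follow-up visit, and to a smaller extent to condom use through seasonal or non-linear change between T0 and T2.

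The bias is about 1.49 points per 1-point shift per period where no matching baseline exists. The false-positive illustration also borrows the variance and ICC assumed for condom use, because the document gives none for care receipt. Everything rests on two-sided alpha, 3 inferred periods and two sequences of 4 clinics. It would be too strong to say that the sponsor chose to ignore calendar time.

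**What to change.** In Efficacy Trial Statistical Analysis and in the Abstract, add categorical calendar period (step, assigned by enrolment date) as a fixed effect in every efficacy model, with its interaction with survey time wherever change is modelled. Set the treatment indicator from each clinic's randomised schedule, and describe the effect as the period-adjusted contrast.

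The text change is a sentence or two. The statistical cost is a larger standard error than the no-period model gives. For level comparisons it is the one that the stated 12.2 points appears to assume (0.0435 against 0.0220). It would be wrong to call the change free, because for the change model precision may be worse or better than 12.2 points depending on the within-person correlation. The power section should therefore state the number of steps and the assumed correlation, and restate the detectable difference for the model actually used.

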#### Quality Control Process Monitoring

The investigative team at the Johns Hopkins School of Medicine, which is serving as the coordinating site for this multi-site randomized controlled trial, is serving as the data management team. This team will communicate any important protocol modifications to relevant parties, as appropriate, and in conjunction with the institutional review board. The investigative team comprises experts in adolescent health, male health, and evaluation research. We are using the World Health Organization’s Monitoring and Evaluating Digital Health Intervention guidelines to inform this study’s process monitoring of system factors, intervention quality, and intervention engagement [56]. We will assess technical functionality and stability through periodic user tests by the study team and routine app data monitoring to confirm the app is functioning as expected. We will assess intervention quality through the 48-hour follow-up survey, which will include questions on usability, acceptability, and satisfaction, including an overall app rating. We will track intervention engagement by monitoring whether participants complete core Health-E You content, opt in rates to share the patient summary with their clinician, time spent on Health-E You, and viewed content. We will provide monthly reports to participating clinics on these metrics and participant enrollment, which will provide an opportunity to gather clinic feedback to understand and address barriers with participant recruitment or sharing the patient summaries with clinicians. We will also collect online surveys before and after the intervention from clinicians and staff at each clinic about clinic workflows and visit times and postintervention about clinicians’ perceived acceptability and usability of and satisfaction with Health-E You to provide contextual information about the trial.

